**Fig. 1 Fig1:**
[figure not shown]
Study algorithm. FiO_2_, fraction of inspired oxygen; FR, flow reduction group; OR, FiO_2_ reduction group; SR, simultaneous reduction group

**Fig. 2 Fig2:**
[figure not shown]
Schedule of enrollment, interventions, and assessments according to the Standard Protocol Items: Recommendations for Interventional Trials (SPIRIT) guideline

### Definitions

Weaning success is defined as a condition in which the patient meets all of the weaning criteria after 24 h of conversion to conventional oxygen therapy. A weaning failure is defined as the patients requiring re-application of the HFNC within 24 h of conversion to conventional oxygen therapy or needing NIV or endotracheal intubation during the HFNC weaning period or within 24 h of conversion to conventional oxygen therapy. If clinical improvement is not seen during follow up, NIV or intubation should be considered according to the clinician’s judgment. Immediate endotracheal intubation will be considered when there are two or more of the following conditions according to standard clinical practice: respiratory rate > 40 breaths/min, arterial pH < 7.2, PaO_2_ < 50 mmHg, signs of high work of breathing such as use of accessory muscle, abdominal paradox, need to secure the airway due to increased sputum, or altered mental status.

### Outcome measures

The primary outcome is time to successful weaning from HFNC after 24 h of conversion to conventional oxygen therapy. The secondary outcomes will include the success or failure to wean off HFNC (within and after 24 h of conventional oxygen therapy), changes of arterial blood gas analyses (PaO_2_, PaCO_2_, and pH), intolerance rate, length of hospital stay, and in-hospital mortality.

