### Study design and patients

This study is a prospective, investigator-initiated, randomized controlled study with three experimental groups. Patients aged over 18 years receiving respiratory support through a HFNC for any indication will be screened for study participation. Participants satisfying all weaning criteria, whether they are medical or surgical, will be prospectively recruited after providing written informed consent. The weaning criteria are as follows: patients who have recovered from their underlying condition, show no signs of respiratory distress (such as agitation, diaphoresis, or anxiety), with arterial pH ≥ 7.35, partial pressure of oxygen (SpO_2_) > 90% with FiO_2_ ≤ 0.5, respiratory rate ≤ 25 breaths/min, heart rate ≤ 120 beats/min, and systolic blood pressure (SBP) ≥ 90 mmHg. Patients will be excluded from the study if they have severe hypercapnia (pH < 7.25), respiratory arrest requiring tracheal intubation, cardiac arrest, acute coronary syndrome or life-threatening arrhythmias, or failure of more than two organs. Patients who have had recent trauma or burns to the neck and face, are pregnant, or who refuse to participate or cooperate in the study will be also excluded.

Informed consent will be obtained from the patients when they are ready to be weaned off the HFNC. However, if the patients cannot understand information about the study, remember the information, or communicate their decision by talking, using sign language, or any other means, they will be considered to be unable to make a decision. In that case, consent will be obtained from their families or the legal representatives.

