### Types of interventions

After randomization, the participants will undergo FR, OR, or SR strategies for weaning off the HFNC. In the FR group, flow will gradually be reduced by 10 L/min/h. When it reaches 20 L/min, FiO_2_ reduction will then begin at 0.1 /h until it reaches 0.3. In the OR group, FiO_2_ will gradually be reduced by 0.1 /h until it reaches 0.3. At this point, flow will be reduced by 10 L/min/h until it reaches 20 L/min. Finally, in the SR group, both flow and FiO_2_ will be gradually reduced simultaneously at a rate of 10 L/min and 0.1 /h, respectively, until they reach the HFNC weaning-off targets (20 L/min for flow and 0.3 for FiO_2_). Weaning will proceed only when the patient satisfies all the weaning criteria at every weaning point. When flow and FiO_2_ reach weaning-off targets, the patient will be transferred to conventional oxygen therapy, such as low-flow nasal prongs.

We have followed the Standard Protocol Items: Recommendations for Interventional Trials (SPIRIT) 2013 statement, which defines the standard protocol items for clinical trials [18] (see Additional file 1). The study algorithm is depicted in Fig. 1 and the SPIRIT schedule is shown in Fig. 2.

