### Clinical and laboratory evaluations

A physical examination, laboratory evaluations, and medication reviews will be conducted before treatment. The laboratory evaluations including the arterial blood gas analysis (ABGA) will be performed based on the usual clinical practice, and additional examinations will be conducted if it is deemed necessary for treatment (irrespective of the study).

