### Statistical analyses

Statistical analyses will be performed on both a per-protocol (PP) and an intention-to treat (ITT) basis. For the PP analysis, all participants who complete the study will be included to evaluate the primary and secondary outcomes. For the ITT analysis, all participants enrolled and randomized to one of the three groups will be included. In the interim analysis, if the *P* value is < 0.003, we will stop the study early, accepting the significance of the outcome. If not, we will recruit the remaining half of the subjects. Sub-group analysis according to the respiratory failure type (hypoxemic or hypercapnic) is planned. Unless otherwise specified, continuous variables will be expressed as mean plus standard deviations or median and categorical variables as percentages. Student’s *t* test will be used to compare continuous variables; the chi-square or Fisher’s exact test will be used to compare categorical variables. Unless otherwise stated, all tests are two-sided and performed at the 0.05 significance level. Analyses will be performed using SPSS 20.0 (IBM Corp., Armonk, NY, USA).

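### Change in raw PaO2 is a between-arm outcome although the flow-first arm is, by design, on a higher FiO2 than the other two arms during weaning

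*Protocol article*

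**What the plan says.** Under Outcome measures, the protocol article names "changes of arterial blood gas analyses (PaO_2_, PaCO_2_, and pH), intolerance rate" as secondary outcomes. Oxygenation is therefore PaO2 as measured. The text gives no PaO2/FiO2 ratio, reference setting or time point.

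Under Types of interventions, the arms change FiO2 in a different order:
- FR lowers flow first. "When it reaches 20 L/min, FiO_2_ reduction will then begin at 0.1 /h until it reaches 0.3".
- OR lowers FiO2 first. "In the OR group, FiO_2_ will gradually be reduced by 0.1 /h until it reaches 0.3", and flow follows.
- SR lowers both together: "in the SR group, both flow and FiO_2_ will be gradually reduced simultaneously at a rate of 10 L/min and 0.1 /h, respectively".

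All arms share one end point: "When flow and FiO_2_ reach weaning-off targets, the patient will be transferred to conventional oxygen therapy, such as low-flow nasal prongs". The targets are 20 L/min and FiO2 0.3.

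The weaning criteria under Study design and patients include an arterial pH of at least 7.35 and "partial pressure of oxygen (SpO_2_) > 90% with FiO_2_ ≤ 0.5". Types of interventions requires all criteria to be met at each weaning point. On timing, Clinical and laboratory evaluations says: "The laboratory evaluations including the arterial blood gas analysis (ABGA) will be performed based on the usual clinical practice". Under Statistical analyses, Student's *t* "test will be used to compare continuous variables"; no allowance for FiO2 or flow is stated.

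**The concern.** PaO2 responds directly to FiO2, and the order in which FiO2 is cut is part of what is randomised. At the same hour of weaning an FR patient can still be on the starting FiO2 while an OR or SR patient has already been lowered. A raw PaO2 drawn then differs between arms even if the lungs do not. Sampling every patient every hour would not remove this.

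The risk is a false signal of impaired oxygenation. The hypothesis is that SR is faster without more weaning failure, and the trial sets out to study safety as well as efficacy. A lower raw PaO2 in SR than in FR could be read as a physiological cost of SR when it shows only a lower setting.

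**Working it through.** **Plan's own figures.** The article gives no figure for the blood gas outcome. Its sample size reproduces as 90 / (1 − 0.10) = 100. It is used here only for the 30 evaluable patients per arm.

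**Inputs from the article.** Steps of 10 L/min and 0.1 FiO2 per hour; targets of 20 L/min and 0.3; FiO2 at most 0.5 at entry; 30 per arm; two-sided 0.05.

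**Assumptions not in the article.** Start flow 50 L/min (starts of 40 and 60 give the same maximum gap in FiO2); no pauses between steps; PaO2/FiO2 of 200-300 mmHg, the same in every arm and constant over time; SD of the PaO2 outcome 15-40 mmHg.

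**Step 1: settings by hour (flow / FiO2), start 50 L/min and 0.5**

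| Hour | FR | OR | SR | FiO2 gap, FR − OR |
|---|---|---|---|---|
| 0 | 50 / 0.5 | 50 / 0.5 | 50 / 0.5 | 0 |
| 1 | 40 / 0.5 | 50 / 0.4 | 40 / 0.4 | 0.1 |
| 2 | 30 / 0.5 | 50 / 0.3 | 30 / 0.3 | 0.2 |
| 3 | 20 / 0.5 | 40 / 0.3 | 20 / 0.3 (target) | 0.2 |
| 4 | 20 / 0.4 | 30 / 0.3 | converted | 0.1 |
| 5 | 20 / 0.3 (target) | 20 / 0.3 (target) | converted | 0 |

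OR and SR have the same FiO2 at every hour until SR reaches target; only flow separates them.

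**Step 2: PaO2 gap with identical gas exchange.** PaO2 = (PaO2/FiO2) × FiO2.
- Gap of 0.1: 200 × 0.1 = 20 mmHg; 300 × 0.1 = 30 mmHg.
- Gap of 0.2 (0.5 against 0.3): at 200, 100 − 60 = 40 mmHg; at 300, 150 − 90 = 60 mmHg.
- Start of 0.4: the gap never exceeds 0.1, so 20-30 mmHg at most. Start of 0.3: no gap.

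Randomisation balances starting FiO2 on average, so the gap in change from baseline equals the gap in the later value. On PaO2/FiO2 it is 0 under these assumptions.

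**Step 3: would a *t* test notice?** Normal approximation: power = Φ(gap / (SD × √(2/30)) − 1.96). At SD 40 the standard error is 40 × √(2/30) = 10.33.
- Gap 40: Φ(3.87 − 1.96) = 0.972. Larger gaps or smaller SDs give more.
- Gap 20: Φ(1.94 − 1.96) = 0.491. At SD 15 the same gap gives 0.999.

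These figures suppose that all 30 patients per arm contribute a gas at that gap, so they are an upper case.

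**Step 4: can such gases enter the comparison?** The article does not tie gases to the common setting. A pH criterion checked at each step suggests gases between start and target. A gas taken by the clock finds the arms at different stages: in the example SR is at target at hour 3, FR and OR at hour 5. A patient who fails during weaning may have a last gas at a setting that depends on the arm.

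**The case against.** The strongest reply is that the article does not say the compared gases are drawn during weaning. No sampling time appears in the text, the schedule figure is not shown, and a window or a derived ratio could sit in the full protocol or analysis plan. Every arm passes through the same 20 L/min and 0.3, where the FiO2 artefact is zero. This stands as a limit: the problem is conditional on mid-weaning gases. It does not dispose of the point, because the outcome is named as raw PaO2, admits any gas, and the pH criterion makes intermediate gases likely.

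The size is also open to challenge. The 40-60 mmHg gap needs a start at 0.5, the highest FiO2 the criteria allow, and sampling in the few hours when the gap is 0.2. That stands, so it is quoted as a maximum.

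A reader might infer three stronger things that the documents do not support:
- *That PaCO2 and pH are distorted too.* FiO2 does not enter PaCO2 directly as it does PaO2. Flow might affect it, but the article gives no figure, and such a change would be a real effect of the assigned strategy.
- *That all arm contrasts are affected.* The FiO2 argument does not separate OR from SR, which is one of the two hypothesised contrasts.
- *That the formal test should use only gases at the common target.* That conditions on reaching the target and drops patients who fail during weaning, against the article's intention-to-treat set. It also relies on gases that the text does not schedule.

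**Conclusion.** The point holds for raw PaO2, for FR against OR or SR, and for gases drawn on HFNC between start and target. There, raw PaO2 would differ by about 20-30 mmHg per 0.1 gap in FiO2, and by up to 40-60 mmHg from a start of 0.5, with no true difference in gas exchange. This rests on an assumed PaO2/FiO2 of 200-300 mmHg that stays constant as FiO2 changes, and on weaning without pauses. How many gases fall in that window cannot be told from the article.

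The outcome is secondary, and no decision or stopping rule is attached to it. The conclusion on time to weaning is unaffected. The change is worth making because it is nearly free and removes a plausible false finding against SR.

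**What to change.** - For gases drawn on HFNC, define the oxygenation outcome as change from baseline in PaO2/FiO2, using the set FiO2 recorded with each gas. Include all randomised patients with a gas, including those who fail during weaning.
- Leave PaCO2 and pH as planned, with set flow and FiO2 recorded beside each value.
- Report gases after conversion to conventional oxygen separately, because no FiO2 is set on nasal prongs.
- Use gases at the common 20 L/min and 0.3 setting only as a supportive comparison.

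Cost: flow and FiO2 must be logged with each gas. No extra blood draws and no change to the weaning rules are needed. PaO2/FiO2 is only an approximate correction for FiO2, so some dependence on the setting may remain. The change does not address which patients happen to be sampled under usual practice.

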### Randomization

A research coordinator will randomize the participants. An independent statistician will generate a list of random numbers. Eligible participants will be randomly assigned at a ratio of 1:1:1 to the flow reduction first (FR) group, the FiO_2_ reduction first (OR) group, or the simultaneous reduction (SR) group, in accordance with the predefined randomization list with a block size of 3. Information about the randomization will not be provided to the research supervisor, co-researcher, or patients. In the case of an emergency, co-researchers who are aware of the random assignments should avoid participating in future results analysis.

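### Length of hospital stay has no stated start; counted from admission, it would include days before randomisation that no weaning strategy can change, and would usually be compared less precisely than it could be

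*Protocol article*

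**What the plan says.** - **Outcome.** The Outcome measures section ends its list of secondary outcomes with "intolerance rate, length of hospital stay, and in-hospital mortality". It names neither a start nor an end for the stay, and no other section of the article does so.
- **Entry.** Under Study design and patients, "Patients aged over 18 years receiving respiratory support through a HFNC for any indication will be screened for study participation". The weaning criteria begin with "patients who have recovered from their underlying condition", and "Informed consent will be obtained from the patients when they are ready to be weaned off the HFNC".
- **Start of the strategies.** Types of interventions states: "After randomization, the participants will undergo FR, OR, or SR strategies for weaning off the HFNC".
- **Allocation.** The Randomization section assigns patients 1:1:1 "in accordance with the predefined randomization list with a block size of 3" and mentions no stratification.
- **Analysis.** Statistical analyses says that Student's *t* "test will be used to compare continuous variables", and that "all tests are two-sided and performed at the 0.05 significance level" unless otherwise stated. It mentions no covariate adjustment.

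**The concern.** Randomisation does not take place at admission. Each participant has first been treated with HFNC, recovered and met the weaning criteria. A stay counted from admission is therefore the sum of a part fixed before allocation and a part that the strategy could influence. The first part carries no information about treatment, but its patient-to-patient variation enters the SD used in the t test. Because any indication is accepted, medical or surgical, that variation could be considerable.

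At stake is the precision of the only resource-use outcome on the list, in a trial that plans 30 evaluable patients per group and names its small size as a limitation. The primary outcome, the hypothesis and the sample size are not affected.

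**Working it through.** **The plan's own figure.** The article gives no SD, effect size or power for length of stay, so there is no figure on this point to reproduce. The only related number, the recruited total, does reproduce: 90 / (1 − 0.10) = 100. It has no bearing on the time origin.

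**Set-up.** Let *pre* be days from admission to randomisation and *post* days from randomisation to discharge. Let r = SD(pre) / SD(post), and let ρ be their correlation. Neither r nor ρ is in the documents, so the values below are assumptions. For stay counted from admission,

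Var(pre + post) = Var(post) × (1 + r² + 2ρr).

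Allocation cannot change *pre*, so the expected difference between groups is the same from either origin and only the standard error (SE) changes. Its factor is √(1 + r² + 2ρr).

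**No correlation (ρ = 0).** The sample needed for equal precision scales with 1 + r², so the effective share of the sample is 1 / (1 + r²).

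| r | 1 + r² | SE factor | Rise in SE | Effective share of sample |
|---|---|---|---|---|
| 0.5 | 1.25 | 1.118 | 12% | 80% |
| 1 | 2.00 | 1.414 | 41% | 50% |
| 2 | 5.00 | 2.236 | 124% | 20% |

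**Sensitivity to correlation (SE factor).**

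| r | ρ = −0.3 | ρ = 0 | ρ = 0.3 |
|---|---|---|---|
| 0.5 | √0.95 = 0.975 | 1.118 | √1.55 = 1.245 |
| 1 | √1.40 = 1.183 | 1.414 | √2.60 = 1.612 |
| 2 | √3.80 = 1.949 | 2.236 | √6.20 = 2.490 |

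The factor falls below 1 when r² + 2ρr < 0, that is when ρ < −r/2. At r = 0.5 the threshold is −0.25, which is why ρ = −0.3 gives a slight gain there.

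**Adjustment as the alternative.** In a linear model with group and *pre* as terms, whole stay and post-randomisation stay give the same group estimate, because they differ only by *pre*. The residual variance is Var(post) × (1 − ρ²). The unadjusted whole-stay variance exceeds this by Var(post) × (r + ρ)², which is never negative. So, apart from the degree of freedom spent, adjustment loses nothing whatever the sign of ρ.

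**False positives.** I simulated 20,000 two-group comparisons with no true difference: 33 per group, log-normal stays with log-SD 0.8, and independent prior stays 0, 0.5, 1 or 2 times as long. The two-sided 0.05 t test rejected in 4.4% to 4.9% of trials. Counting from admission does not raise the error rate.

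**How large an effect could be.** The weaning criteria require FiO2 ≤ 0.5, and the strategies lower it by 0.1 per hour to 0.3, so there are at most (0.5 − 0.3) / 0.1 = 2 hourly FiO2 steps. Uninterrupted sequential weaning takes the flow steps plus the FiO2 steps, and simultaneous weaning takes the larger of the two. The direct saving is the smaller of the two, so at most about 2 h. If post-randomisation stay were 2 to 5 days (an assumption), 2 h would be 2/48 = 4.2% to 2/120 = 1.7% of it.

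**The case against.** The strongest objection is that the article never says the stay is counted from admission. It is a condensed report, the schedule figure is not reproduced in the text at hand, and the full protocol or analysis plan may define the origin or add a covariate. That stands. The point depends on the ordinary meaning of the term, and a missing definition in an article is not by itself an error.

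Four stronger readings are tempting, and the documents do not support them.

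- **Bias.** A reader might infer that an imbalance in prior stay would distort the comparison or create spurious effects. Randomisation balances prior stay in expectation, and the SE of the t test already contains its variation. The error rate holds, as the simulation shows.
- **A large loss of power.** A reader might pair the SE factors with a sizeable treatment effect and report a large fall in power. The direct saving is only about 2 h. For effects of that order (ratios of 0.958 and 0.983 in the same simulation), rejection was 4.4% to 5.0% from either origin, no different from the significance level. Effects through held steps or weaning failure could be larger, but the article gives no figure for them.
- **Long, widely varying prior stays.** The entry criteria show that time passes before randomisation. They do not show how much, or how variable it is. A short postoperative course of HFNC could bring a patient in early.
- **An inevitable loss.** A sufficiently negative correlation cancels or reverses it.

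Whole-admission stay is also a conventional measure, so reporting it is not a mistake. What remains is that a comparison between randomised groups is better made on the part of the stay that allocation can influence.

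**Conclusion.** The point holds as a minor improvement to one secondary outcome. On the ordinary reading, days fixed before randomisation enter the outcome and, with no adjustment stated, would usually widen its confidence interval. The SE factor is √(1 + r² + 2ρr). With no correlation the rise is 12%, 41% or 124% at r = 0.5, 1 or 2, and it vanishes when ρ is below −r/2. Both r and ρ are assumed, so the actual size cannot be stated. Because any direct effect on stay is probably small, the gain is a tighter interval and not a likely change in the conclusion. My confidence is moderate, because the full protocol may already count from randomisation.

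**What to change.** In Outcome measures, define the secondary outcome as length of hospital stay from randomisation to discharge. Alternatively, keep the whole stay and adjust the comparison for days from admission to randomisation. Report days from admission to randomisation by group as a baseline characteristic, and keep whole-admission stay as a descriptive line.

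The cost is one line of wording. The article does not say expressly which dates are recorded. However, the time of randomisation is known by design, and measuring hospital stay and in-hospital mortality already requires follow-up to discharge, so no new data collection should be needed. The small downside is that the headline figure is no longer the conventional whole-admission stay; the descriptive line covers that. If the full protocol already counts from randomisation, only the article's wording needs to be aligned with it.

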### Sample size calculation

It is difficult to calculate the target number of patients, because this is the first RCT evaluating the best strategy for weaning off the HFNC. Considering that 30 patients were compared in the NIV weaning protocol study, we estimate that a total of 90 participants, 30 in each group, would be needed. A total of 100 participants will be recruited in anticipation of a 10% dropout rate in each group based on the recent HFNC weaning study [17]. We have prepared for one interim analysis at the time when half of the subjects have completed the study.

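### Length of hospital stay is compared by t test in all randomised patients, so an in-hospital death is scored by its day of death as if it were a discharge

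*Protocol article*

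**What the plan says.** Under Outcome measures, the protocol article ends its list of secondary outcomes with "length of hospital stay, and in-hospital mortality". These are two separate outcomes, and no composite joins them.

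Under Statistical analyses, one method is given for each type of variable. Student's t "test will be used to compare continuous variables", and "the chi-square or Fisher’s exact test will be used to compare categorical variables". The first covers length of stay and the second covers mortality. The qualifying phrases in that section concern how variables are described, and the sidedness and level of the tests. Neither makes an exception for length of stay.

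On who is analysed: "For the ITT analysis, all participants enrolled and randomized to one of the three groups will be included". And: "For the PP analysis, all participants who complete the study will be included to evaluate the primary and secondary outcomes". The article does not say whether a patient who dies counts as having completed the study. Nowhere does it limit length of stay to survivors, treat death as a competing event, or give deaths a worst value.

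**The concern.** A hospital stay can end in discharge or in death. A t test on the number of days cannot tell them apart: a death on day 7 and a discharge home on day 7 contribute the same value. Where arms differ in mortality, part of any difference in mean stay then reflects how many patients died and when, not how quickly patients recovered.

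This is a different problem from skewness. A log transformation, or a rank test on the same day counts, would still score an early death as a short stay.

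The per-protocol analysis does not resolve it. If deaths count as completers, the problem stays. If they are dropped, the comparison is restricted to those who survived, a group formed after randomisation.

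What is at stake is the reading of one secondary outcome. The Discussion says that several clinical outcomes will be compared in order to suggest the best strategy, so length of stay is meant to carry some weight.

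**Working it through.** **The plan's own figures.** The article states no mortality rate, mean stay or standard deviation, so there is no length-of-stay figure to reproduce. From the sample size section only the group size is used here: "we estimate that a total of 90 participants, 30 in each group, would be needed". The recruitment total follows from it (90 / 0.9 = 100), and nothing below depends on that total.

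**Formula.** Suppose the stay of survivors (mean L) and the time to death (mean D) have the same distribution in both arms, and only mortality differs (pA, pB). Then

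mean stay in an arm = (1 - p) × L + p × D

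difference, B minus A = (pB - pA) × (D - L).

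The sign is set by whether deaths come before or after typical discharge. The size is set by the mortality difference and that gap in days.

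**Simple illustration (all inputs assumed).** L = 20 days; mortality 10% in A and 20% in B.
- Death at day 8: A = 20 × 0.9 + 8 × 0.1 = 18.8; B = 20 × 0.8 + 8 × 0.2 = 17.6; difference -1.2 days.
- Death at day 10: A = 19.0; B = 18.0; difference -1.0 day.
- A reversal: let survivors in B stay 20.5 days instead of 20, with death at day 8. B = 20.5 × 0.8 + 8 × 0.2 = 18.0, against 18.8 in A. B is worse on both stay among survivors and mortality, yet its mean stay is 0.8 days shorter.

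**Range over the timing of death (all inputs assumed).** Survivors' stay is lognormal with median 14 days and log-SD 0.7, identical in both arms. Time to death is lognormal with the same log-SD and the median shown. Each mean is the median × exp(0.7²/2) = median × 1.278, so L = 17.9 days. The simulated columns come from a two-arm Student's t test, 30 per arm, 20,000 runs, at two-sided 0.05.

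| Median day of death | Mortality A v B | Difference by formula (days) | Simulated difference (days) | B shorter on average | B significantly shorter |
|---|---|---|---|---|---|
| 5 | 10% v 20% | 0.1 × (6.4 - 17.9) = -1.15 | -1.2 | 64% | 5.4% |
| 7 | 10% v 20% | 0.1 × (8.9 - 17.9) = -0.9 | -0.9 | 60% | 4.5% |
| 14 | 10% v 20% | 0 | 0.0 | 50% | 2.2% |
| 20 | 10% v 20% | 0.1 × (25.6 - 17.9) = +0.8 | +0.8 | 42% | 1.4% |
| 5 | 10% v 30% | -2.3 | -2.3 | 75% | 10.3% |
| 7 | 10% v 30% | -1.8 | -1.8 | 70% | 7.2% |
| 20 | 10% v 30% | +1.5 | +1.6 | 35% | 0.8% |

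Without distortion, the last column should be close to 2.5%. It was 2.2% to 2.4% in the simulations with equal mortality of 10% in both arms. With 33 per arm the results are much the same.

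**Would the mortality comparison give a warning?** The two assumed mortality differences correspond to 3 v 6 deaths and 3 v 9 deaths among 30 per arm. Fisher's exact test gives two-sided p = 0.47 and p = 0.10. Imbalances of this size would be visible in the table but would not be flagged by the planned test.

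**The case against.** Four arguments can be made against the point.

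- **It rests on silence.** Length of stay is only named, not defined. The t test reaches it through a general rule, and a condensed article may leave the handling of deaths to a fuller document. What remains is that the article does fix a method and an analysis set, and the two together score a death as a discharge. A fuller document may refine this, but the stated rule would still have to change.
- **Deaths may be few.** A reader might infer from the mortality outcome, and from the Discussion's remark on critically ill patients, that many deaths are expected. The documents do not support that. The eligibility criteria admit patients who have recovered from the underlying condition, show no respiratory distress and have stable vital signs, and they exclude failure of more than two organs. A doubling of mortality is an assumption here, as are the lengths of stay. This stands: the distortion may turn out to be small.
- **The direction is not fixed.** A reader might also infer that the arm with more deaths always looks better. It does not. The shift vanishes when deaths come at the typical time of discharge and reverses when they come later.
- **The consequence is limited.** It is tempting to say that the trial would choose the wrong strategy. The Hypothesis section rests on time to weaning and weaning failure, and mortality is reported beside length of stay. That stronger reading is not supported. The side-by-side report is only a partial safeguard, since in about 30 patients per arm a real imbalance in deaths can easily be non-significant while the mean stay is taken at face value.

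**Conclusion.** The point holds as a flaw in how one secondary outcome is analysed. Under the stated rules, length of stay mixes recovery with death, and any mortality difference between arms carries over into the comparison of stay. Under the assumed 10% v 20% mortality with identical stays among survivors, the shift runs from about -1.2 days (deaths around day 5) through zero (deaths around day 14) to about +0.8 days (deaths around day 20). The chance of a falsely significant shorter stay in the higher-mortality arm is at most about twice the nominal 2.5% in that case. It reaches about 10% only with 10% v 30% mortality and early deaths. All of these inputs are assumptions. If mortality is similar across arms and death times are alike, there is no distortion in the comparison. The primary conclusion and the sample size are unaffected. It is worth correcting because the remedy is cheap and can be settled before the data are analysed.

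**What to change.** Exempt length of hospital stay from the general t test rule and adopt one of the following in the intention-to-treat set.

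- **Time from randomisation to discharge alive, with in-hospital death as a competing event.** Report the cumulative incidence of live discharge by arm. Deaths should not simply be censored at the day of death, since that treats them as patients who could still go home.
- **A rank comparison with deaths ranked worst.** Every in-hospital death is placed below the longest stay that ended in discharge alive, and the arms are compared by a rank test.

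In either case, present and interpret the result together with in-hospital mortality. Stay among survivors may be shown as well, labelled descriptive.

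The cost is a sentence or two of analysis text and slightly more analysis work. The result is also less simple to explain than a difference in mean days. The article does not list the dates collected, but the end date of the stay and whether the patient left alive are already needed for the two listed outcomes, so no extra data should be required. The sample size does not change.
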